## Abstract

**Background:**

Falls are common in frail older adults and often result in injuries and hospitalisation. The Nintendo^® ^Wii™ is an easily available exercise modality in the community which has been shown to improve lower limb strength and balance. However, not much is known on the effectiveness of the Nintendo^® ^Wii™ to improve fall efficacy and reduce falls in a moderately frail older adult. Fall efficacy is the measure of fear of falling in performing various daily activities. Fear contributes to avoidance of activities and functional decline.

**Methods:**

This randomised active-control trial is a comparison between the Nintendo WiiActive programme against standard gym-based rehabilitation of the older population. Eighty subjects aged above 60, fallers and non-fallers, will be recruited from the hospital outpatient clinic. The primary outcome measure is the Modified Falls Efficacy Scale and the secondary outcome measures are self-reported falls, quadriceps strength, walking agility, dynamic balance and quality of life assessments.

**Discussions:**

The study is the first randomised control trial using the Nintendo Wii as a rehabilitation modality investigating a change in fall efficacy and self-reported falls. Longitudinally, the study will investigate if the interventions can successfully reduce falls and analyse the cost-effectiveness of the programme.

**Trial registration:**

Australia and New Zealand Clinical Trials Register (ANZCTR): ACTRN12610000576022

## Background

In Singapore, there is an increasing growth of older adults (300,000) and the prevalence of falls is high with a reported incidence of 129000 per year by the Singapore Ministry of Health in 2007. The common consequences of these falls are fractures and soft tissues injuries that may lead to significant disability [1]. Fractures managed in an acute care setting contribute to rising healthcare cost [2-5]. In addition minor trauma and soft tissue injuries lead to activity avoidance and embeds the fear of further falling psychologically [6].

A previous experience of fall may subsequently cause fear in the older person who will then self-restrict mobility or will depend on others for activities of daily living (ADLs) [7]. Fear of falling significantly contributes to functional decline [7] and the health and well-being of the older person [8-10]. In order to quantify the fear of fall, fall efficacy scales have been developed to assess the perceived confidence of the older population [11-13].

Contribution to frailty is a history of sedentary lifestyle in the older population which results in strength and balance impairment [7,14-16]. There are numerous interventions in rehabilitation to modify fall risk and reverse these impairments. There are many research that addressed rehabilitation in the frail population [16-24]; however those that improve fall efficacy significantly are scarce [25]. The Nintendo Wii system has been postulated to be effective in improving functional performance by enhancing flexibility, balance, strength and coordination training [26]. The additional advantage of the Nintendo Wii system is the visual feedback that the participant receives during the training session. This visual feedback aids the participants to improve balance [27], while the game simulation creates a perception that they can perform high level activities.

## Objectives

### Primary research hypothesis

The Nintendo Wii group intervention is more effective than the gym-based group intervention in improving fall efficacy and self-reported falls in the older adult aged 60 and above.

### Secondary research hypothesis

The Nintendo Wii group intervention is more effective than the gym-based group intervention to improve the secondary outcome measures: knee extension strength, timed up and go (TUG) test, 6-minute walk test (6MWT), narrow corridor walk (NCW) test, gait speed, Short Form -- 36 version 2 (SF-36v2) questionnaire and European Quality of Life -- 5 dimensions (EQ-5D) questionnaire.

## Methods

### Design

This is a parallel prospective single-blind randomised active-control trial. The ratio of subjects in each group is 1:1; refer to Figure 1 for the flow of participants in our study (week 0 to week 13). Each participant who completes the week 13 follow-up will be given a pedometer to track daily physical activity from week 13 to 24 and a final assessment is conducted on week 24. During the first 13 weeks, participants report weekly on incidence of falls to the interventionist. From week 14 to 52, participants record incidence of fall on a falls history sheet kept at home and to report the falls to the Principal Investigator or the outcome assessor immediately. The outcome assessor will contact the participants monthly from week 14 to 52 to update on any fall incidence.

**Figure 1 F1:**
[figure not shown]
**Participant flow**. SOC: Specialist Outpatient Clinic LIFE: Lifestyle Improvement Fitness Enhancement

### Participants

The participants are patients from the Singapore General Hospital (SGH) Specialist Outpatient Centre Geriatric Medicine department, SGH Lifestyle Improvement Fitness Enhancement Centre Osteoporosis and Bone Metabolism unit, SGH Physiotherapy Falls Clinic and public volunteers. The volunteers are approached to participate in the study within the hospital premises. The screening of eligible participants is done by a medical doctor or a physiotherapist during consultation sessions. The abbreviated mental test is used to screen for cognitive impairment [28], while the Short Physical Performance Battery (SPPB) is used to stratify frailty [29]. The scores from the AMT and SPPB include or exclude participants from the study.

The inclusion criteria of this study:

• Age 60 years old and above

• Community dwelling

• Independent in ambulation (with or without walking stick assist)

• Have fear of falls in daily activities

• Able to commit 12 weeks of supervised intervention

• Score of SPPB from 5 to 9 (moderately frail)

• Speaks or understands English, Mandarin or local dialects

The exclusion criteria of this study:

• Permanent bedbound status

• Disabled in ambulation

• Significant cognitive disorder (AMT score below 7 for 60-74 years old, below 6 for 75 years old and above)

• Untreated medical conditions

• End-stage illness or disease and/or life expectancy less than a year

• Unstable cerebral haemorrhage in the past 3 months

• Fractures in healing phase

• Surgery in the past 3 months, unless with surgeon's approval

• Pulmonary embolism or deep vein thrombosis in the past 3 months

Participants who are eligible and agree to register for our study will be assessed in the SGH Physiotherapy department for baseline measures by an independent outcome assessor.

### Ethics and withdrawals

This study has been approved by the SingHealth Centralised Institutional Review Board D (Reference: 2010/177/D) in accordance with the International Conference on Harmonisation (ICH)/Singapore Guidelines for Good Clinical Practices (GCP). Written informed consent is obtained from the participant using the forms from the ICH/Singapore Guidelines for GCP. The principal investigator of our study is [name], a physiotherapist with Singapore General Hospital.

Participants have the right to withdraw from the study at any time during the trial, but are encouraged to complete the trial after randomisation to minimise drop-out rate. In the event of adverse change of medical condition in the participant deemed unsafe to continue with the study by the principal investigator or co-investigators, the trial for the participant will be terminated.

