### Sample size

Our primary endpoint is a change in MFES scores immediately post-intervention. There was no literature of MFES investigated in the moderately frail population. We estimated the minimum clinically important difference (MCID) to be detected between the novel intervention programme and the traditional supervised exercise programme and derived a change in 1.5 MFES units. Previous randomised controlled trial showed no change in MFES scores post intervention because healthy volunteers were recruited in their study [25]. The use of healthy volunteers resulted in a ceiling effect in that trial. In the absence of trials assessing MFES in the moderately frail older adults, we assumed a common between-participant standard deviation of 2 units for MFES [25]. This translates to a standardized effect size of interest (Cohen's ***d***) of 0.75. Accordingly, the required sample is 30 participants per group for a two-tailed comparison of the groups when ***d ***is 0.75, power is 0.8 and type I error is 0.05. Considering a 15% drop-out rate, 80 participants will be recruited.

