### Statistical methods

Missing data will be analysed by intention-to-treat approach. Baseline measures for age, body mass index, MFES, TUG test, 6MWT, PPA knee extension strength, NCW test, SF-36v2 and EQ-5D will be analysed for normality. The primary outcome measure is the change in MFES score. Outcome measures will be quantitatively analysed with the mixed model for between group comparisons for statistically significant difference. Statistical significance is set at *p*(2-tailed) < 0.05. Clinical significance will also be analysed based on MCID or minimal detectable change for each of the outcome measures. The mean MCID will be obtained from participants who have a rating of 3 on the GROC scale.

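### The medical stopping rule ends the participant's whole trial, not only the exercise, and intention-to-treat cannot make up for outcomes that are then not collected

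*Protocol article*

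**What the plan says.** All references are to the protocol article.

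- **Ethics and withdrawals.** The trigger is an "adverse change of medical condition in the participant deemed unsafe to continue with the study by the principal investigator or co-investigators". The consequence is that "the trial for the participant will be terminated". Voluntary withdrawal is covered separately in the same section. Nothing is said about outcome collection after termination.
- **Statistical methods.** "Missing data will be analysed by intention-to-treat approach". Separately, "Outcome measures will be quantitatively analysed with the mixed model for between group comparisons". The article does not connect the mixed model to the missing data.
- **Design.** Falls are collected in two phases: "During the first 13 weeks, participants report weekly on incidence of falls to the interventionist"; later, "The outcome assessor will contact the participants monthly from week 14 to 52 to update on any fall incidence", alongside immediate self-report.
- **Primary research hypothesis.** It covers both endpoints: "improving fall efficacy and self-reported falls in the older adult aged 60 and above".
- **Sample size.** The primary endpoint is the MFES change immediately after the intervention, and the authors "derived a change in 1.5 MFES units" as the difference to detect, with an assumed SD of 2 and 15% drop-out.

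**The concern.** Stopping a participant's exercise and stopping that participant's follow-up are different decisions. The stopping sentence makes no distinction and speaks of the trial as a whole. Followed literally, it ends measurement for randomised participants selected on medical grounds. An intention-to-treat analysis needs outcomes from just such people, so the rule works against the principle that Statistical methods invokes. The wording there adds to the problem by offering an analysis-set principle as if it were a way of handling missing values.

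The loss may be informative. The Background names fractures and soft-tissue injuries as common results of falls and says that a fall can leave a person fearful and less mobile. The exclusion criteria bar people whose fractures are still healing. An injurious fall is therefore a foreseeable reason for termination, and it bears on both later falls and fall efficacy. At stake are the week-13 and week-24 MFES and any falls after the stopping event. The falls also feed the one-year cost-effectiveness analysis.

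**Working it through.** **1. The plan's own figure.** Inputs from Sample size: difference 1.5, SD 2, two-sided alpha 0.05, power 0.80. The normal approximation gives n per arm = 2 × (1.96 + 0.84)² × 2² / 1.5² ≈ 27.9, so 28. The t-test version gives 28.9, so 29. The stated 30 is reproduced closely enough. A 15% loss from 80 leaves 68, or 34 per arm, with power 0.86 (t-test) to 0.87 (normal). Precision is not the problem and the sample size need not change. The question is bias.

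**2. What is lost, by time of termination.**

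| Terminated | Lost if the sentence is followed as written |
|---|---|
| Before week 13 | Week-13 MFES (primary), week-24 MFES, all later falls |
| Weeks 13 to 24 | Week-24 MFES, all later falls |
| Weeks 24 to 52 | Later falls only |

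A fall that itself leads to termination would usually be on record already, through the weekly reports or the later immediate reports and monthly calls.

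**3. What the mixed model can do.** It uses incomplete records and is valid under missing at random. A participant stopped before week 13 has no post-baseline MFES. If the response is the change score, that participant contributes nothing; otherwise, only a baseline value. Validity then rests on these participants doing no worse than the model predicts for their arm and baseline.

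**4. Size of the bias (assumed figures, not in the document).** Let p be the proportion terminated before week 13 and D the amount by which their true MFES change falls short of what the analysis assumes for them. The mean over everyone randomised to an arm is then lower than the analysed mean by p × D, so

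bias in the group difference = p₁D₁ − p₂D₂, which is D × (p₁ − p₂) when D is the same in both arms.

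| Terminated, arm v arm | D = 1 | D = 2 | D = 3 |
|---|---|---|---|
| 15% v 15% | 0 | 0 | 0 |
| 10% v 20% | 0.1 | 0.2 | 0.3 |
| 5% v 25% | 0.2 | 0.4 | 0.6 |

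The arm with more terminations looks better than it should. At 10% v 20% the bias is 0.1/1.5 = 7% to 0.3/1.5 = 20% of the target difference. Equal rates do not guarantee zero: at 15% in both arms with D₁ = 3 and D₂ = 1, the bias is 0.15 × 3 − 0.15 × 1 = 0.3.

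Each row averages 15%, or 12 of 80, so the table treats all planned drop-out as medical termination before week 13. That is generous to the concern.

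**5. Falls.** The article gives no expected fall rate or termination rate for the trial, so the number of falls lost after stopping cannot be sized.

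**The case against.** The strongest reply has four parts.

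- **The trigger is narrow.** Only a change judged unsafe for continuing leads to termination. A reader might infer that anyone with an adverse medical change is removed, and that the fallers therefore vanish from the data. The document does not support this: many falls would not meet the test, and the triggering fall is normally recorded. What may be lost is later falls and later MFES.
- **The end of follow-up is read from silence.** Design says that participants are contacted monthly and states no exception, and a condensed article may leave post-discontinuation procedures to a fuller protocol. This has some weight. But the sentence on the page ends the trial for the participant, which invites site staff to stop contact.
- **The mixed model is named, and details of missing-data handling belong in an analysis plan.** This is fair. A reader might say that missing at random fails here; the document shows only that it may. The absence of a detailed missing-data strategy is not the point. The point is a sentence that misnames intention-to-treat and a rule that stops collection. No analysis plan can recover data that were never gathered.
- **Nothing points to unequal termination.** Both arms share the instructor, the session timings and an equivalent home programme. They differ in a 20-minute component, and those who decide on termination are not said to be blinded, so a difference is possible but not indicated. A reader might take a bias of 10 to 20% of the target effect as the expected size. It needs an unsourced split, such as 8 v 4 of 12 drop-outs, with every drop-out medical. With 34 per arm the standard error is 2 × √(2/34) ≈ 0.49, so 0.1 to 0.3 units is about 0.2 to 0.6 of a standard error.

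**Conclusion.** The point holds in a limited form. As worded, the stopping sentence ends outcome collection along with the programme for participants stopped as unsafe, and this is in tension with the intention-to-treat approach. The two are not in flat contradiction, because everyone can still be analysed as allocated with some values missing. The missing-data sentence is wrong as worded, since it names an analysis set rather than a method.

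Informative missingness is a reasonable inference from the article's own account of what falls do, not something that it states. Bias in the comparison requires termination, or its relation to outcome, to differ between arms. On the assumed figures it ranges from zero to a few tenths of an MFES unit against a target of 1.5. This could shift the estimate but would not by itself overturn a 1.5-unit effect. The defect merits correction because it is avoidable at small cost and cannot be repaired at the analysis stage.

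**What to change.** 1. **Ethics and withdrawals.** Leave the clinical decision to stop as it stands. Add that stopping the programme does not stop data collection: unless the participant withdraws consent, the week-13 and week-24 MFES interviews (by telephone if needed) and the falls contacts to week 52 continue. For weeks 1 to 13, say how falls are reported once a participant no longer attends sessions.
2. **Statistical methods.** Replace the missing-data sentence. State that all randomised participants are analysed in the arm to which they were allocated, using the mixed model under a missing-at-random assumption.
3. **Sensitivity analysis.** For participants stopped for medical reasons whose MFES is still missing, repeat the primary comparison with their change set worse by a range of fixed amounts, for example 1 to 3 units, including a case in which the amount differs between arms. The range is a choice to be agreed, not a figure from the article.

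**Cost.** Two wording changes, a few extra telephone interviews and one extra analysis. The MFES is already administered by interview and monthly contact already exists, so existing staff can do this. The sample size is unaffected.

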### Interventions

The interventions are carried out at a satellite clinic to prevent unblinding of the outcome assessor. The two interventions are on separate days to minimise the chance of interaction between the participants from the different groups. The interventions were developed through an evidence-based approach. A physiotherapist with 3 years of clinical experience and American College of Sports Medicine clinical exercise specialist certification conducts the interventions for both groups with adherence to the intervention protocol.

The home exercise programme is equivalent in both groups. Exercise bands for resistance training at different difficulty levels are issued to each participant according to the baseline assessments for the first 6 weeks and the next level of band is issued on the seventh attendance.

One of the unique features of the study is that it has a component of participant specific management in both intervention arms. This enables achievement of the participant's goals in rehabilitation. Every participant may present with different impairments that will need to be addressed with specific strengthening exercises, balance and coordination training, agility training or acute pain management.

#### Novel intervention arm

The Nintendo Wii programme is incorporated with exercises that are taught as home exercises. In this study, the WiiActive game is used that includes exercise band resistance training, balance and coordination training, calisthenics, and cardiovascular training. The duration of a session is one hour including the rest interval, with the following breakdown: 10 minutes of stretching exercises, 20 minutes of WiiActive game play, 15 minutes of home exercises education, and 15 minutes of participant specific management.

#### Traditional intervention arm

Supervised exercises in a gym setting include resistance band training, balance and coordination training, calisthenics, and cardiovascular training. The duration of a session is one hour including the rest interval, with the following breakdown: 10 minutes of stretching exercises, 20 minutes of cardiovascular training, 15 minutes of home exercises education, and 15 minutes of participant specific management.

Participants are to attend once per week of supervised exercises and carry out home exercises at least twice per week. Exercise log sheets and home exercise handouts are issued to each participant on the first intervention session and the log sheets are collected on the last intervention session. Compliance to the programme is monitored by the attendance rate [30].

Home safety and modification advice is provided in a handout for each participant [31]. The details of the handout are shown in Table 1.

**Table 1 T1:** Home safety and modification

Locations	Modifications
Living room	Ensure that wires and cords are out of the way.
	
	Arrange furniture so that you can move around easily and safely.
	
	Remove carpets and rugs that are along your walking path.

Kitchen	Try to make sure that items are easily accessible to avoid reaching for them.
	
	Wires and cords should not be in your path.
	
	Clean all spills immediately.

Self-care	If you wear shoes at home, use rubber-soled shoes.
	
	Ensure you use a walking aid as necessary.
	
	Make sure you go for regular medical and eye check-ups.
	
	Take your medications as prescribed.
	
	Be aware of the side-effects of the medications you are taking.

Bathroom	Install grab rails on walks.
	
	Place non-slip mats in the shower area.
	
	Use a shower chair and a portable shower head when showering.
	

Bedroom	Place light switches within reach of your bed.
	
	Have night lights between the bathroom and the bed.
	
	When getting out of bed, sit and wait a while before standing up to avoid getting dizzy.
	

Stairways	Keep stairway free of clutter.
	
	Install handrails on one or both sides of the stairs if possible.

PPA: Physiological Profile Assessment, SPPB: Short Physical Performance Battery, MFES: Modified Fall Efficacy Scale, Short FES-I: Short Fall Efficacy Scale -- International, 6MWT: 6-minute walk test, TUG: Timed-up-and-go, NCW: Narrow corridor walk, SF-36v2: Short form -- 36 version 2, EQ-5D: European Quality of Life -- 5 dimensions, GROC: Global rating of change

### Baseline data

Demographics are obtained via the assessor on the first assessment session. Baseline demographics include age, gender, ethnic group, living status (staying alone or with family), history of falls in the past 12 months, number of medications, height, weight, resting heart rate, resting blood pressure, AMT, SPPB score and Physiological Profile Assessment (PPA) fall risk score.

### Outcomes

The outcome measures are assessed one week before the first intervention session (week 0), one week after the last intervention session (week 13) and a final reassessment on week 24 by an independent blinded outcome assessor (Table 2). The primary outcome of this study is an improvement in fall efficacy with the Modified Falls Efficacy Scale (MFES). New recent falls after the initiation of intervention will investigate the success of the programme in falls prevention. This is carried out by self report of falls by the participants via telecommunication and on a falls recording sheet. The secondary outcomes of this study are improvement in knee extensor strength, endurance, agility, functional status and quality of life. The global rating of change (GROC) scale is used to assess the participant's perceived change from baseline on each follow-up [32,33].

**Table 2 T2:** Data collection time-points

Data	Baseline	Week 13	Week 24	Week 52
Demographics	**X**			
Fall history	**X**	**X**	**X**	**X**
Fall risk (PPA)	**X**	**X**		
Frailty (SPPB)	**X**	**X**		
Fall efficacy (MFES, Short FES-I)	**X**	**X**	**X**	
Strength (knee extension)	**X**	**X**	**X**	
Endurance (6MWT)	**X**	**X**	**X**	
Agility (TUG)	**X**	**X**	**X**	
Dynamic balance (NCW)	**X**	**X**		
Gait speed (4 m walk)	**X**	**X**	**X**	
Quality of life (SF-36v2*, EQ-5D)	**X**	**X**	**X**	
Participant's perceived change (GROC)		**X**	**X**	
Home exercises (Exercise diary)		**X**		
Physical activity (Pedometer)			**X**	

*Week 24 SF-36v2 components assessed are physical function and bodily pain

Fear of fall (self efficacy): MFES is a validated 14-item questionnaire of fall efficacy of the older person in various ADLs and community activities [11]. It is administered by an interviewer approach in our study to prevent misinterpretation by the participant and to maintain consistent and accurate responses from the participant. The Short Fall Efficacy Scale -- International questionnaire takes a shorter time to administer with 7-item on indoor and outdoor activities [13]. The questionnaires have no risk of recall bias as they require the participants to rate their perceived confidence based on the day of assessment.

Strength (impairment): Knee extension strength measurement with the PPA is a maximum isometric contraction on a spring gauge [34]. The test is conducted 3 times with a rest interval of 30 seconds. Another strength measurement is the weight lifted for 10 repetitive maximum knee extension of 0 to 90°.

Endurance (functional limitation): 6MWT is one of the most commonly conducted field tests and is utilised in numerous research trials for the evaluation of aerobic capacity [35]. The test is carried out on a clear and quiet 10-metre corridor marked with a cone at each end. Instructions are given prior to the test and the time left to the end of the test is announced by the assessor at interval of 1 minute.

Functional status (functional limitation): TUG is an established test of agility in the older population and is used in this study for agility changes [36-38]. Subject is to rise from the chair and walk 3 metres, marked by a cone, and return to the seat. Higher functional task is assessed in our study using the NCW test -- a test of dynamic balance that comprises of a 6-metre walk within the width of 0.2-metre throughout the entire course [39]. Gait speed is calculated from 4-metre walk test of SPPB [15,29], which is potentially a sixth vital sign [40].

Quality of life (disability): Quality of Life will be measured with the SF-36v2 [41] and EQ-5D questionnaires [42].

